## **2. Introduction**

### **2.1. Purpose of the Statistical Analysis Plan**

The purpose of the SAP is to give a detailed elaboration of the statistical analysis planned to be executed on primary and secondary outcomes etc. corresponding to the primary and key secondary objectives in the BELIEVE Cohort study [1]. This SAP was developed after the study protocol was registered and published [2] and before database closure and conduct of any statistical analyses. Deviations from the pre-specified study protocol are summarized and explained in the SAP (section 4.2.).

Reporting of the study will follow the STROBE- (Strengthening the Reporting of Observational Studies in Epidemiology) and TRIPOD-guidelines (Transparent Reporting of a multivariable prediction model for Individual Prognosis Or Diagnosis), adhering to the guidelines for reporting of cohort studies [3, 4].

### **2.2. Background and rationale**

Chronic inflammatory diseases (CID) are a diverse set of immunological diseases that include diseases of the gastrointestinal tract (Crohn's disease [CD] and ulcerative colitis [UC]), musculoskeletal and connective tissue (rheumatoid arthritis [RA], axial spondyloarthritis [axSpA] and psoriatic arthritis [PsA]) and the skin (psoriasis [PsO]). CIDs are recurring lifelong illnesses of potentially early onset that can substantially affect the life quality of patients and their families [5-7]. Furthermore, they are prevalent diseases and the disease burden is predicted to rise [8-11]. CIDs pose a heavy burden on the community due to direct health-related costs (largely influenced by providing biological medications[11]) as well as indirect costs associated with patient's reduced productivity and sick-leave. CIDs are frequently treated with biologic drugs that target pro-inflammatory cytokines, e.g., tumor necrosis factor (TNF). However, up to 60% of the patients do not benefit from such biological therapy [11-13].

The increasing incidence of chronic inflammatory diseases in the Western world has prompted research into the potential impact of lifestyle (smoking, physical activity, urban living etc.), and many have been associated with risk of developing CIDs, including diet [14-19]. Accordingly, many patients ask their healthcare professionals for lifestyle recommendations that can influence the effectiveness of treatment. However, in a recent systematic review examining the impact of diet on TNF inhibitor (TNFi) response, it was concluded that the evidence is scarce and more research is needed [20]. Thus, we commenced on this prospective cohort study to identify dietary factors that support optimal treatment outcomes of biologic therapy. Specifically, as specified in the published protocol [2], we wanted to explore the impact of intake of fibers and red/processed meat on treatment outcomes.

### **2.3. Aim**

The overall aim is to explore the prognostic value of dietary patterns on response to treatment in patients with CIDs initiating treatment with a biological agent.

### **2.4. Hypotheses**

We hypothesize that a diet high in fiber *AND* low in red/processed meat are associated with better treatment outcomes.

Additional hypotheses are that 1) low intake of red/processed meat and 2) high intake of dietary fibers, are independently associated with better treatment outcomes and 3) a potential interaction between them may further improve treatment outcomes.

## 2.5. Objective

To examine if treatment outcomes in patients with CID vary with dietary differences.

Primary objective: To compare the differences in clinical response following high intake of fiber *AND* low intake of red/processed meat, relative to a low intake of fiber *AND* high intake of red/processed meat, on the proportion of individuals achieving a clinical response (defined individually according to their specific condition) after a period of 14-16 weeks, in patients with CID.

Key secondary objectives: To compare the differences in clinical response following high intake of fiber *AND* low intake of red/processed meat, relative to a low intake of fiber *AND* high intake of red/processed meat, on changes in measures of health-related quality of life and disability (SF-12 physical component summary [PCS] and mental component summary [MCS], and the short health scale components), C-reactive protein (CRP), physician global assessment, and patient global assessment from baseline to week 14-16, as well as the proportion of individuals continuing biologic therapy at week 14-16, in patients with CID.

Exploratory secondary objectives: (i) To compare the effect of high intake of fiber relative to a low intake of fiber while adjusting for meat intake, on the proportion of individuals achieving a clinical response (defined individually according to their specific condition) after a period of 14-16 weeks, in patients with CID; (ii) To compare the effect of low intake of red/processed meat, relative to a high intake of red/processed meat while adjusting for fiber intake, on the proportion of individuals achieving a clinical response (defined individually according to their specific condition) after a period of 14-16 weeks, in patients with CID.

## 3. Study methods

### 3.1. Study design

BELIEVE is an observational multi-center cohort study with prospective enrollment of CD, UC, RA, axSpA, PsA and PsO patients initiating treatment with a biologic agent (or switching to another). Treatment with biologics was assigned to the patients independent of BELIEVE and their habitual diet. When a patient was found to be a candidate for initiation of biologic treatment or switching to another biologic agent, they were invited to participate in the study. Patients were examined at two time points; at baseline and 14-16 weeks after treatment initiation, according to Danish clinical standards. The examination program included questionnaires (including a Food Frequency Questionnaire at baseline), clinical assessment and sampling of blood, urine, feces and intestinal biopsies (the latter only for UC and CD). The inclusion period was between 1st of September 2017 and 31st of March 2020 with follow-up until end of July 2020. The following centers in Denmark participated in inclusion of patients to BELIEVE: Department of Hepatology and Gastroenterology, Aarhus University Hospital; Diagnostic Centre, Silkeborg Regional Hospital; Department of Gastroenterology, Herlev and Gentofte Hospital; Medical Department, Hospital Sønderjylland; Department of Gastroenterology, Hospital of South West Jutland; Department of Medical Gastroenterology, Department of Rheumatology and Department of Dermatology and Allergy Centre, Odense University Hospital.

### 3.2. Sample size and power considerations

Deciding on sample size is a well-known difficulty with exploratory prognostic factor research studies. To obtain an adequate number of outcome events, we applied 'the rule of thumb', whereby 10 outcomes are needed for

each independent variable. We planned to enroll 320 patients in total with the anticipation that 50% of these would experience a clinical response within the 14–16 weeks period after initiation of biological therapy. With this in mind and anticipating that we would observe at least 160 events (i.e., clinical response among the 320 patients), the study would be sufficiently powered to explore the impact of as many as 16 independent variables including condition and clinical center. Since using the ‘rule of thumb’ method to justify sample size is a debated practice, we went one step further and estimated the statistical power to detect differences between two dietary groups. For the contrast between groups and for a comparison of two independent binomial proportions (those with high-fiber, low-meat intake vs. other) using Pearson’s  $\chi^2$  statistic, with a  $\chi^2$  approximation, with a two-sided significance level of 0.05 ( $P < 0.05$ ), a total sample size of 318—assuming an ‘allocation ratio’ of 1 to 2 (one-third)—has an approximate power of 0.924 (i.e., >90% statistical power) if the anticipated proportions responding to therapy are 60% and 40%, respectively. However, due to pre-specified time constraints, inclusion to BELIEVE was terminated on 03-30-2020 before reaching the planned sample size of 320 patients in total.

### **3.3. Statistical interim analyses and stopping guidelines**

No statistical interim analyses were planned or executed.

### **3.4. Timing of final analysis**

The final analysis will be conducted after completion of the 14-16 week follow-up visit of the last patient included in the study (ultimo July 2020) and after completion of the SAP, approved and revised by the research team and collaborators. The present SAP pertain to the primary publication and analysis from the BELIEVE cohort study. Biological samples collected in BELIEVE (beside C-reactive protein [CRP]) are part of more exploratory objectives and the results will be presented in separate coming peer reviewed papers.

### **3.5. Timing of outcome assessments**

As described in the pre-specified protocol [2], patients are examined at two time points; at baseline and 14-16 weeks after treatment initiation, where primary endpoints are evaluated.

Taking the COVID-19 pandemic into account, we have decided to allow a window of +/- 4 weeks for outcome assessment in order to prevent missing outcomes.

## **4. Statistical principles**

### **4.1. Statistical significance and confidence intervals**

All P values and 95% confidence intervals will be two sided. We will not apply explicit adjustments for multiplicity, rather we will interpret the analysis of the key secondary outcomes according to the Hochberg sequential procedure [21]: The analyses of the key secondary outcomes will be performed, and the correspondent P values will be ordered from largest to smallest in a list. If the largest P value is less than the significance level of 0.05, then all the tests are considered significant. In contrast, if the largest P value fails to show statistical significance, then progressively more stringent P values are applied as a significance level (the second largest P values: 0.05/2, the third largest: 0.05/3 and so on). When a test succeeds to show a statistically significant difference, then the remaining tests downstream from this are considered significant. Thus, comparisons continue until a test shows a statistical difference or until all comparisons are made. The key secondary statistical tests will be reported with P values for hypothesis tests and claims of potential statistical significance. Further, due to potential issues of multiplicity as multiple tests will be performed, we will interpret ‘statistically significant’ findings in the context of whether the 95% confidence interval (CI) excludes outcomes that could be perceived as clinically important.

## 4.2. Protocol deviations

### *Eligibility criteria*

**Protocol:** Eligible patients are patients diagnosed with a CID, including CD, UC, RA, axSpA, PsA, PsO, Hidradenitis Suppurativa (HS) and non-infectious Uveitis (niU) that are initiating biological therapy targeting TNF, who are naïve to biologics.

### **SAP modifications:**

- 1) There were no patients with Hidradenitis Suppurativa and Non-infectious Uveitis included in the study.
- 2) Patients initiating all kinds of biological therapy were enrolled instead of only TNFi therapy\*.
- 3) In addition, patients that previously have received biologic treatment were also made eligible\*.

*\*We will apply these new strata in subsequent sensitivity analyses*

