## 6.2. Analysis methods

The baseline characteristics of the participants (table 1) will be summarized for each dietary exposure profile (HFLM and LFHM) using descriptive statistics. Data will be presented as either means and standard deviations (SDs), or medians and interquartile ranges (IQRs) for continuous outcomes, and numbers and percentages for binary outcomes.

The primary outcome is the proportion of patients with a clinical response to therapy 14-16 weeks after treatment initiation. Response is defined for each CID (see section 6.1.1.). The number and proportion of participants who achieved treatment response will be summarized based on dietary profile (fig. 2 and table 2). We will investigate the association between dietary profile at baseline (HFLM and LFHM) and treatment response (yes/no) on the ITT population using logistic regression models. A simple (unadjusted) logistic regression model, an adjusted model (adjusted for type of CID, clinical center, age, sex, smoking) and a propensity adjusted model (further adjusted for propensity score) will be presented in table 2. The Odds ratio (OR) of achieving clinical response at week 14-16 for CID patients in HFLM group (the upper 33.3 % of the study population based on the ratio of fiber to meat intake) versus the LFHM group (the lower 66.6 %) will be reported along with the 95 % confidence interval (CI) and two-sided p-value (fig. 2 and table 2). We will also perform similar analyses on the key secondary outcome measures (see 6.1.2.), corresponding to our pre-specified key secondary objectives.

Secondary explorative analyses will include repeating the logistic regression models for treatment outcomes using secondary predictors of interest; 1) the upper 33.3% (high fiber; HF) vs. the lower 66.6% (low fiber; LF) of the study sample with respect to intake of dietary fibers (adjusted for meat intake), and 2) the lower 33.3% (low meat; LM) vs. the upper 66.6% (high meat; HM) of the study sample with regard to red/processed meat intake (adjusted for fiber intake). In addition, a possible interaction between the lower 33.3% of the sample

with respect to red/processed meat intake and the upper 33.3% of the sample with regard to fiber intake will be examined using logistic regression with same covariates as stated above.

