## 6.4. Sensitivity analyses

Where complete cases and multiple imputation analyses give different results, the analyst should attempt to understand why, and this should be reported in publications [52]. Robustness is a concept that refers to the sensitivity of the overall conclusions to various limitations of the data, assumptions, and analytic approaches to data analysis. Robustness implies that the treatment effect and primary conclusions of the trial are not

substantially affected when analyses are carried out based on alternative assumptions or analytic approaches. For the purpose of sensitivity, multiple sensitivity analyses will be performed to assess the robustness of the primary analyses. For instance, a simplistic 'single step, null responder imputation' would represent a conservative base case and is potentially valid even if data is 'missing not at random' as it assumes and implies that patients have not improved or worsened after entering the study. When there are missing outcome data for our dichotomous outcomes we will explore "best" and "worst" case scenarios by replacing missing values with "good" outcomes in one group and "bad" outcomes in the other group. Sensitivity analyses will include analyses based on:

- 1) complete case analysis,
- 2) a 'non-responder-imputation',
- 3) the 'per protocol population',
- 4) the population meeting the unmodified eligibility criteria  
(exclusion of patients initiating treatment with biologics targeting other agents than TNF and patients previously treated with biologics).

Results of the sensitivity analyses are presented in the Appendix, table 2. When the different sensitivity analyses are in agreement, and the analyses on the sensitivity analyses and the main analysis lead to essentially the same conclusions, confidence in the trial results is increased.

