**Clinical examination**

Physician global assessment (0-100 mm VAS), median (IQR)  
CRP, mean (SD), mg/L

\*Will be estimated by comparing groups using the standardized mean difference (SMD); an SMD above 0.5 SD-units will be evaluated as a potential (data driven) confounding variable. HFLM; High fiber/low meat (exposed), LFHM; low fiber/High meat, CID; Chronic Inflammatory Disease, NSAID; Non-steroidal Anti-Inflammatory Drugs, PROs; patient reported outcomes, HRQoL; Health related quality of life, SF-12; 12-item Short Form survey, PCS; physical component summary, MCS; mental component summary, VAS; visual analog scale, CRP; C-reactive protein

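### Previous biologic use enters the primary population through the widened eligibility but is not a pre-specified covariate, and the one sensitivity analysis on the widening cannot separate treatment history from drug class

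*SAP*

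**What the plan says.** Section 4.2 (Eligibility criteria) gives the protocol population as biologic-naive patients starting a TNF inhibitor. The SAP modifications admit starters of any biologic and patients treated with biologics before. The stated reason is to enlarge the study population. A note to both changes reads: "We will apply these new strata in subsequent sensitivity analyses".

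Section 4.3 defines the ITT population as everyone who consented and answered the food frequency questionnaire (FFQ), so both added groups are in the primary analysis.

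Section 6.1.4 names sex, age and smoking as the variables to test for confounding, with CID type and clinical center as further adjusting variables. Section 6.2 plans a simple model, "an adjusted model (adjusted for type of CID, clinical center, age, sex, smoking"), and a third model that adds the propensity score. The Table 2 footnotes repeat this list.

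Section 6.4, item 4, is the only planned analysis that addresses the widening. It specifies "exclusion of patients initiating treatment with biologics targeting other agents than TNF and patients previously treated with biologics". The Appendix Table 2 footnote says the sensitivity analyses are adjusted in the same way as the primary one.

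Table 1 has a row for the number of previous biologics (0, 1, 2, at least 3). Its footnote says that "an SMD above 0.5 SD-units will be evaluated as a potential (data driven) confounding variable". There is no row for the class of the biologic being started.

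**The concern.** The population changed and the covariate list did not change with it. Section 6.1.4 defines a confounder as a variable that causes the outcome, probably causes the exposure, and is not an effect of either. Previous biologic use comes before the baseline FFQ, which covers the past month. It could plausibly lower the chance of response and could plausibly have altered diet. If so, it meets the SAP's own definition, and part of a difference in treatment history between HFLM and LFHM patients could appear as a diet effect in the primary odds ratio.

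The sensitivity plan also delivers less than the note in section 4.2 suggests. That note speaks of strata, in the plural. Section 6.4 has one run that drops both groups at once. If its result differs from the main result, the reader cannot tell whether treatment history, drug class or the smaller sample is responsible. It also gives no estimate in the patients who were added.

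**Working it through.** **1. The plan's own figure.** Section 3.2 gives the design used below: "a total sample size of 318", an allocation "of 1 to 2 (one-third"), "with a two-sided significance level of 0.05", and the stated power holds "if the anticipated proportions responding to therapy are 60% and 40%, respectively". That is 106 HFLM and 212 LFHM patients.

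- Pooled response = (106 × 0.60 + 212 × 0.40)/318 = 0.467.
- Null SE = √(0.467 × 0.533 × (1/106 + 1/212)) = 0.0593.
- Alternative SE = √(0.24/106 + 0.24/212) = 0.0583.
- Power = Φ((0.20 − 1.96 × 0.0593)/0.0583) = 0.924, as stated.

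The power statement is therefore sound. The point concerns covariates, not sample size.

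**2. Can the SMD rule catch an imbalance in previous use?** For a yes/no factor, SMD = (p₂ − p₁)/√{[p₁(1 − p₁) + p₂(1 − p₂)]/2}.

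- Assumed 30% (HFLM) against 50% (LFHM): 0.20/√((0.21 + 0.25)/2) = 0.42, below 0.5.
- Assumed 30% against 40%: 0.21.
- To reach 0.5, the LFHM share must be about 42.5% if HFLM is 20%, 54% if HFLM is 30%, and 64% if HFLM is 40%.

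The rule is applied to the observed SMD, so chance matters. Simulating 30% against 50% with 106 and 212 patients, the observed SMD exceeds 0.5 in about 26% of samples. The rule would miss that imbalance about three times in four.

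**3. How far could the crude odds ratio move?** The SAP gives neither the share of experienced patients by diet group nor response by treatment history, so all inputs are assumptions. Take no diet effect, response rₙ in naive and rₑ in experienced patients, and an experienced share p in each diet group. Response in a group is (1 − p)rₙ + p·rₑ. For 60%/40% response and 30% against 50% experienced:

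- HFLM: 0.7 × 0.60 + 0.3 × 0.40 = 0.54
- LFHM: 0.5 × 0.60 + 0.5 × 0.40 = 0.50
- OR = (0.54/0.46)/(0.50/0.50) = 1.17

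The last column is the chance of a two-sided P below 0.05 with 106 and 212 patients, using the normal approximation of step 1.

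| Response naive/experienced | Experienced HFLM/LFHM | SMD | Crude OR | P < 0.05 |
|---|---|---|---|---|
| 55%/45% | 30%/40% | 0.21 | 1.04 | 5% |
| 60%/40% | 30%/40% | 0.21 | 1.08 | 6% |
| 65%/35% | 30%/40% | 0.21 | 1.13 | 8% |
| 55%/45% | 30%/50% | 0.42 | 1.08 | 6% |
| 60%/40% | 30%/50% | 0.42 | 1.17 | 10% |
| 65%/35% | 30%/50% | 0.42 | 1.27 | 17% |

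These are crude values. The planned adjustment for CID type and center could reduce them. If the imbalance ran the other way, so would the bias.

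**4. What can analysis 4 show?** Section 3.2 says enrolment ended short of 320, and the number left after the joint exclusion is not given. By the formula of step 1, power for 60% against 40% is 0.81, 0.67 or 0.45 if 70%, 50% or 30% of 318 remain (assumed). Agreement with the main result would be partial reassurance. Disagreement could not be assigned to either change.

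**The case against.** **Drug class.** A reader might infer that class of biologic confounds the diet comparison in the same way. The SAP does not support that. Diet is reported for the month before treatment starts, so a drug chosen afterwards cannot have caused it, and section 3.1 states that biologics were assigned independently of habitual diet. Class could be linked to diet only through shared causes such as treatment history. It matters mainly as an outcome predictor or effect modifier. This objection stands.

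**Previous use may still reach a model.** The SAP prints no closed list of propensity-score terms, and previous biologics fall under the SMD rule. It would be too strong to say that the variable can never enter or that the rule never fires. But the named candidates do not include it, and the footnote says only that a variable is evaluated, without naming a model or saying how an SMD is formed over four categories. An SMD over the four levels could be larger than the yes/no value. The route is contingent, not pre-specified.

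**Analysis 4 already answers the question.** Within the population meeting the unmodified criteria, neither history nor class can vary, so this is a real robustness check. It does not adjust the full-population estimate or identify the source of a difference.

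**The size is assumed.** That is so. The central case, log OR 0.16, is less than one standard error (about 0.24 at 106 and 212 patients) and small beside the design target (OR 2.25, log 0.81). That earlier treatment marks harder-to-treat disease or changes diet is a plausible argument, not a statement in the SAP.

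**Parameters are scarce.** Section 3.2 allows 16 variables at 160 events. Five terms for CID type, five to seven for center (six hospitals or eight departments), three for smoking, and one each for age, sex and diet already make 16 to 18. This argues for using the propensity score, not for omitting the variable.

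**Conclusion.** The point holds for previous biologic use. The primary population includes experienced patients, no pre-specified covariate list includes their treatment history, and the one contingent route would usually miss an imbalance of the size illustrated. Confounding of the primary odds ratio is possible, not shown. Under the assumed inputs (no diet effect, 30% against 50% experienced, response 55%/45% to 65%/35%), the crude OR would be about 1.08 to 1.27; at 30% against 40% it would be 1.04 to 1.13. These ranges precede adjustment for CID type and center, and no figure in the SAP fixes their size or direction.

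On the sensitivity plan, analysis 4 is a valid but partial check that cannot separate the two eligibility changes. The weakness is worth correcting before analysis, when the choice of covariates is still blind to results. It does not invalidate the design.

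**What to change.** - Pre-specify previous biologic use (0 versus at least 1) as a covariate of the adjusted model, or as a propensity-score term to spare parameters, whatever its SMD in Table 1. State the choice in sections 6.1.4 and 6.2 and in the Table 2 footnotes.
- Keep class of the started biologic out of the propensity score, because it is chosen after the reported diet.
- Keep sensitivity analysis 4 and add two runs: biologic-naive patients only, and TNF-inhibitor starters only.
- Show the HFLM effect descriptively in naive and in experienced patients, without a claim of significance.

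This is a change of SAP wording. The number of previous biologics is already planned for Table 1, and the class of agent is already needed for analysis 4. The cost is one more coefficient (none in the outcome model if the variable goes in the score) and two extra sensitivity runs with limited power.
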